# Strategy for Withdrawal of Pharmacological Treatment for Urinary Incontinence in Children (StayDry): Protocol for an Open-Label Prospective Randomized Trial

**DOI:** 10.2196/63226

**Published:** 2025-07-09

**Keywords:** urinary incontinence, withdrawal, children, solifenacin, mirabegron

## Abstract

**Background:**

To the best of our knowledge, no studies have investigated the withdrawal strategy of pharmacological treatment with solifenacin or mirabegron in children diagnosed with urinary incontinence who have achieved continence on pharmacotherapy.

**Objective:**

The primary objective is to investigate if abrupt withdrawal versus gradual withdrawal of pharmacotherapy (solifenacin or mirabegron) influences the risk of recurrence of incontinence, assessed by a self-reported 14-day calendar of incontinence episodes.

**Methods:**

Children aged 5-14 years diagnosed with urinary incontinence, treated with pharmacotherapy of solifenacin or mirabegron and ready for withdrawal, will be randomized 1:1 to either abrupt or gradual withdrawal, according to the medical treatment that the child is receiving. The primary outcome measure is the recurrence of incontinence after withdrawal, 1 month after initiation of withdrawal of the physician-prescribed medication, assessed by a self-reported 14-day calendar of incontinence episodes. In addition, recurrence of incontinence after 3, 6, and 12 months after initiation of withdrawal will be measured. The hypothesis that gradual withdrawal is superior to abrupt withdrawal regarding the risk of recurrence of incontinence will be analyzed by logistic regression.

**Results:**

Recruitment began at the end of May 2024 and will continue until 216 patients are included, which is expected by December 2027. As of February 2025, a total of 25 participants are included.

**Conclusions:**

The results are expected to influence the withdrawal strategy of pharmacological treatment with solifenacin or mirabegron in children with daytime urinary incontinence.

**Trial Registration:**

ClinicalTrials.gov NCT06465576; https://clinicaltrials.gov/search?term=NCT06465576

**International Registered Report Identifier (IRRID):**

DERR1-10.2196/63226

## Introduction

### Background

Urinary incontinence is a common condition, affecting up to 21% of children aged 5 to 7 years [1-4], and 4.5% of children and adolescents aged 11-16 years [3,4]. The most common cause of urinary incontinence is an overactive bladder [2,5]. The International Children’s Continence Society defines overactive bladder as a condition with urinary urgency with or without urinary incontinence among children and adolescents aged 5 years and older and without competitive pathology explaining the symptoms, such as neurogenic detrusor overactivity or urinary tract infection [6].

First-line treatment of urinary incontinence is urotherapy, aiming at improving the bladder reservoir function and voluntary bladder control [2]. If urotherapy is insufficient for achieving continence, second-line treatment in most clinical settings is the addition of pharmacological treatment aiming at suppressing bladder smooth muscle contraction [2].

In Denmark, the current stepwise pharmacological therapy consists of an antimuscarinic as solifenacin, or a beta3-adrenoreceptor agonist as mirabegron. If monotherapy of solifenacin or mirabegron is without effect, the child is treated with a combination of solifenacin and mirabegron. However, the pharmacological treatment with solifenacin and mirabegron of children with urinary incontinence is only sparsely investigated.

In children with daytime urinary incontinence, solifenacin and mirabegron have demonstrated efficacy in reducing daytime incontinence episodes [7-13]. Solifenacin and mirabegron are widely used off-label in the pediatric population, and only a few studies dealt with the efficacy and tolerability of the agents [7-10,14].

The pharmacological handling of pediatric incontinence is considered temporary, and withdrawal attempts are recommended after continence has been achieved [15]. There is no generally accepted withdrawal strategy for solifenacin or mirabegron in children. Currently, 2 different withdrawal strategies are being used in the clinical setting, namely abrupt withdrawal and gradual withdrawal, where the dosage prescribed is reduced or the interval between dosages given is increased.

Studies report on the differences in withdrawal strategies of antidiuretic therapy targeted at enuresis in pediatric populations, indicating that gradual withdrawal of desmopressin therapy results in prolonged intervals of continence without relapse [16-19]. One study has reported that gradual withdrawal of solifenacin is superior to abrupt withdrawal in adults [20]. However, to the best of our knowledge, no studies have investigated the strategy of withdrawal of pharmacological treatment with solifenacin or mirabegron in children diagnosed with urinary incontinence who have achieved continence on these pharmaceuticals.

Our study is proposed to ensure an evidence-based approach to a withdrawal strategy for pharmacological treatment with solifenacin or mirabegron in children with urinary incontinence.

### Objectives

The primary objective is to investigate if abrupt withdrawal versus gradual withdrawal of pharmacotherapy (solifenacin or mirabegron) influences the risk of recurrence of incontinence, assessed by a self-reported 14-day calendar of incontinence episodes. We hypothesize that gradual withdrawal is superior to abrupt withdrawal regarding the risk of recurrence of incontinence.

## Methods

### Trial Design

This is an open-label, prospective randomized trial, allocating participants to each of the 3 pharmaceutical groups, according to the physician-prescribed medical treatment that the child is receiving (solifenacin, mirabegron, or solifenacin in combination with mirabegron; Textbox 1). Within each pharmaceutical group, the participant will be randomized 1:1 to the intervention being compared: either abrupt withdrawal or gradual withdrawal. The study duration for each participant will be 12 months and encompasses 1 virtual meeting and 4 follow-up phone consultations.

Overview of the pharmaceutical groups, according to the physician-prescribed medical treatment.
**Solifenacin**
1A: abrupt withdrawal.1B: gradual withdrawal.
**Mirabegron**
2A: abrupt withdrawal.2B: gradual withdrawal.
**Solifenacin + mirabegron**
3A: abrupt withdrawal.3B: gradual withdrawal.

### Eligibility Criteria

The inclusion and exclusion criteria for this study are provided in Textbox 2.

Inclusion and exclusion criteria.
**Inclusion criteria**
The participants’ custody holders must voluntarily sign and date an informed consent before initiation of any study-specific procedures.Age 5 to 14 years old (inclusive) at the time of signing the consent and inclusion.Diagnosed with urinary incontinence as per The International Children’s Continence Society criteria.Pharmacological treatment with solifenacin or mirabegron.Continence has been achieved in pharmacological therapy with solifenacin or mirabegron.Previously, withdrawal attempts were accepted.Continence remained on the same dosage of medication for a minimum of 3 months.Continence remained for a minimum of 3 months (defined as urinary incontinence maximum 1 time a month or less during the last 3 months), self-reported by the participant and the participant’s custody holders.
**Exclusion criteria**
The inability of the patents or parental custody holders to understand the Danish written and oral information.Neurogenic detrusor overactivity (neurogenic bladder).

### Intervention

Eligible children will be randomized 1:1 to either abrupt or gradual withdrawal of the physician-prescribed medication (solifenacin or mirabegron), the children have been treated with before entering the study. Abrupt withdrawal indicates stopping the prescribed medication on the date of withdrawal initiation. Gradual withdrawal involves taking the prescribed applied dosage of the medication every other day over 14 days, with the complete cessation of the medication occurring 14 days after the gradual withdrawal process begins.

### Withdrawal of Participants and Criteria of Discontinuation of Study

A study participant should be withdrawn from the study if at any time one of the following criteria applies:

Recurrence of incontinence during the course of the study (defined as >2 episodes of incontinence assessed by a 14-day calendar of incontinence episodes).It is the wish of the participant (or their parents or parental custody holder[s]) for any reason (withdrawal of informed consent).The discretion of the investigator is for safety reasons.Severe compliance with study procedure as described in the protocol, as judged by the investigator.The investigator judges it as necessary due to medical reasons.Participants with a condition or a situation that, in the investigator’s opinion, may put the participant at significant risk or may interfere significantly with the participant’s participation in the study.Participants with any other condition or situation that, in the investigator’s opinion, may be valid for discontinuation from the study.

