### Secondary Outcome

Secondary outcome measures are as follows. Development of symptoms occurring after abrupt withdrawal of the prescribed medication (solifenacin or mirabegron), assessed by self-reported questionnaires on listed symptoms, as a change from baseline up to 30 days after initiation of withdrawal. Development of symptoms occurring after gradual withdrawal of the prescribed medication (solifenacin or mirabegron), assessed by self-reported questionnaires on listed symptoms, as the change from baseline up to 44 days after initiation of withdrawal. Refer to the Multimedia Appendix 1 for the listed symptoms. The questionnaires are constructed by the authors and do not validate or apply CHERRIES (Checklist for Reporting Results of Internet E-Surveys) items.

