### Procedures During the Trial

The participant timeline is illustrated in Table 1.

**Table 1 table1:** Schedule of assessment.

Visit	Visit 1 (baseline)	Visit 2	Visit 3	Visit 4	Visit 5 (end of study)
Day	0	30	91	182	365
Visit schedule window	—^a^	±5 days	±5 days	±5 days	±5 days
Type of consultation	Virtual	Phone call	Phone call	Phone call	Phone call
Informed consent	✓	—	—	—	—
Inclusion and exclusion criteria	✓	—	—	—	—
Background information incl. demographics	✓	—	—	—	—
Randomization	✓	—	—	—	—
14-day calendar with incontinence episodes	—	✓	✓	✓	✓

^a^Not applicable.

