Follow-up phone consultations with the coordinating investigator or the site investigator are planned 1, 3, 6, and 12 months following initiation of withdrawal. Data collected at the follow-up visits are the status of continence. The participant will fill out a 14-day calendar of incontinent episodes before each visit. Recurrence of incontinence (defined as >2 episodes of incontinence assessed by a self-reported 14-day calendar of incontinence episodes) or no recurrence of incontinence will be registered.

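### Study exit on recurrence at about day 30 cuts short the symptom follow-up that runs to day 44 in the gradual arm

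*Protocol article*

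**What the plan says.** The section on withdrawal of participants and discontinuation opens: "A study participant should be withdrawn from the study if at any time one of the following criteria applies". The first criterion is: "Recurrence of incontinence during the course of the study (defined as >2 episodes of incontinence assessed by a 14-day calendar of incontinence episodes". The exit is from the study, not only from a treatment step.

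The section on Visits 2, 3, 4, and 5 states that follow-up calls "are planned 1, 3, 6, and 12 months following initiation of withdrawal" and that "The participant will fill out a 14-day calendar of incontinent episodes before each visit". Table 1 places Visit 2 at day 30 with a window of 5 days either side. Recurrence is therefore first registered between days 25 and 35.

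The Secondary Outcome section measures symptoms in the abrupt arm "as a change from baseline up to 30 days after initiation of withdrawal" and in the gradual arm "as the change from baseline up to 44 days after initiation of withdrawal". The Intervention section describes the gradual schedule "with the complete cessation of the medication occurring 14 days after the gradual withdrawal process begins". Each arm is thus meant to have 30 days of symptom follow-up after complete cessation: days 0 to 30 and days 14 to 44.

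No sentence exempts the symptom questionnaires from the exit rule. Two other places agree that children with recurrence leave. The Statistical Analysis section fits the later models to the shrinking group still in the study, and Strengths and Limitations presents the removal of relapsed children as part of the pragmatic design.

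**The concern.** A stated exit rule collides with a stated outcome window. In the gradual arm the rule takes effect before the symptom window closes, and it selects on the primary outcome. After Visit 2, gradual-arm symptoms are known only for children in whom no recurrence was recorded.

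The missing days all fall after complete cessation, which is the period the longer window was set up to cover. If children whose incontinence returns also have more symptoms after stopping, the late symptom picture after gradual withdrawal would look milder than it is, and this is the strategy the trial expects to be superior. A descriptive analysis does not remove the problem, because the percentages would rest on a selected denominator. No analysis plan can recover questionnaires that were never collected.

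**Working it through.** **Inputs.** Visit 2 at day 30 ± 5 (Table 1). Symptom window to day 30 (abrupt) and day 44 (gradual) (Secondary Outcome). Cessation at day 0 and day 14 (Intervention). Recurrence of 40% abrupt and 10% gradual, 216 children in total (Sample Size Calculation). Allocation 1:1. I count Visit 2 from the start of withdrawal, as the follow-up text does.

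**1. The plan's own figure.** For 40% against 10%, two-sided 0.05, 80% power, no continuity correction:

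n per arm = [1.96 × √(2 × 0.25 × 0.75) + 0.84 × √(0.40 × 0.60 + 0.10 × 0.90)]² / 0.30² ≈ 31.5, so 32.

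That is 64 per drug group. 64 / 0.90 = 71.1, so 72, and 3 × 72 = 216. The stated figures reproduce. Across drug groups each withdrawal arm has 216 / 2 = 108 children.

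**2. Days lost by a child who leaves at Visit 2.** Gradual: 44 − visit day. Abrupt: 30 − visit day, not below 0.

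| Visit 2 | Gradual: days lost | Gradual: post-cessation days observed | Abrupt: days lost |
|---|---|---|---|
| Day 25 | 19 | 11 of 30 | 5 |
| Day 30 | 14 | 16 of 30 | 0 |
| Day 35 | 9 | 21 of 30 | 0 |

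**3. Size over the whole arm, at the plan's rates.** Children with recurrence: 0.10 × 108 = 10.8 gradual and 0.40 × 108 = 43.2 abrupt. Post-cessation child-days per arm: 108 × 30 = 3,240.

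| Visit 2 | Gradual child-days lost | Abrupt child-days lost |
|---|---|---|
| Day 25 | 10.8 × 19 = 205 (6.3%) | 43.2 × 5 = 216 (6.7%) |
| Day 30 | 10.8 × 14 = 151 (4.7%) | 0 |
| Day 35 | 10.8 × 9 = 97 (3.0%) | 0 |

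About 97 of 108 gradual-arm children remain in the late window.

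**4. Higher recurrence in the gradual arm (assumed).** The share of child-days lost is the recurrence rate × days lost / 30. At 20%, 21.6 children and 6.0% to 12.7% of child-days. At 30%, 32.4 children and 9.0% to 19.0%.

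**5. Where the arm totals cross.** For a common exit day d between 14 and 30, the totals are equal when 43.2 × (30 − d) = 10.8 × (44 − d). Dividing by 10.8 gives 120 − 4d = 44 − d, so d = 25.3. With later exit the gradual arm loses more in total; with earlier exit the abrupt arm does.

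**6. Possible bias, on assumed values only.** Suppose late symptoms occur in 20% of gradual-arm children without recurrence and 40% of those with it. At 10% recurrence the true rate is 0.9 × 20% + 0.1 × 40% = 22%, while 20% is observed. At 40% recurrence the true rate is 0.6 × 20% + 0.4 × 40% = 28%, again with 20% observed. If the two groups have equal symptom rates, there is no bias.

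**The case against.** The strongest reply has five parts.

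- **The timetable is not shown.** The number and timing of questionnaires are in Figure 1, and the listed symptoms are in Multimedia Appendix 1. The lost days are calendar time and could amount to a single questionnaire. Continued completion after exit cannot be excluded. This limits certainty about the amount lost, but the visible text gives no exception to the exit rule.
- **The outcome is secondary and descriptive.** Symptoms are defined separately by arm and no between-arm test is stated. A reader might infer that the main result is compromised. It is not, because recurrence at Visit 2 is itself the primary 1-month outcome.
- **The loss is small overall.** A reader might take the 9 to 19 of 30 days as the loss for the whole gradual arm. It applies only to children with recurrence, and those children still contribute 11 to 21 post-cessation days. Nor are the remaining children simply those who did well, since a child with one or two episodes stays in.
- **The arm difference is not fixed.** A reader might infer that the rule always costs the gradual arm more. Per child it does, but at the plan's rates the arm totals are about equal with exit at day 25, and the abrupt arm loses more with earlier exits, which the rule allows by applying at any time.
- **The direction of bias is assumed.** Nothing in the article links recurrence to the listed symptoms. Days after a restart of medication also no longer describe symptoms after stopping, so ending observation there can be defended. That supports flagging such days rather than leaving them uncollected.

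These points reduce the size and certainty of the concern. They do not remove the conflict between the exit rule and the day-44 window.

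**Conclusion.** The point holds in a limited form. As written, recurrence registered at Visit 2 ends follow-up before the gradual-arm symptom window closes. A child so affected loses 9 to 19 of 30 post-cessation days, against 0 to 5 in the abrupt arm, and late gradual-arm symptoms are described only in children without recorded recurrence.

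The size is modest at the plan's 10% rate and grows if recurrence is higher. That is possible, because the article takes its rates from desmopressin studies for lack of alternatives. The documents do not support a claim of known bias towards milder symptoms or of an arm difference that holds whatever the exit day.

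The conclusion assumes that exit follows at Visit 2, that questionnaires stop at exit, and that all 108 children per arm otherwise complete them.

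**What to change.** Reconcile the discontinuation section with the Secondary Outcome section. State that recurrence does not end symptom data collection: a child with recurrence keeps completing the electronic questionnaires already scheduled, to the end of that arm's window. Record the date of any restart of medication and flag later days. Summarise symptoms in all randomised children, with the flagged days identifiable. Clinical care after recurrence is left to the treating physician.

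The cost is a short amendment to a trial that is authorised and has recruited since May 2024 (25 children by February 2025), including a statement on any enrolled child who has already left on recurrence. Affected families would complete a few more questionnaires. No new visit is needed.

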### Questionnaire on Withdrawal Symptoms

During the study period, participants will be instructed to complete electronic questionnaires regarding withdrawal symptoms associated with the withdrawal of medication. The number of times and when the participant must complete the questionnaire is dependent on the allocated withdrawal method (Figure 1). The questionnaires can be completed with assistance from the parents.

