### Strengths and Limitations

The strength of our study is the randomized multicenter design, encompassing 5 pediatric departments across Denmark. This ensures broad applicability and relevance in daily clinical practice. The study is embedded into and reflects daily clinical practice. The pragmatic design ensures the timely inclusion of patients and excludes participants with relapses of urinary incontinence.

The main limitation is the lack of blinding, which could introduce bias by influencing outcome assessment or potentially introducing placebo effects. Without blinding, investigators and participants are aware of withdrawal allocation, which can lead to biased behavior while answering the questionnaires and data interpretation. Another limitation is no background knowledge about socioeconomic factors.

By conducting the study in real-life settings with medication that is familiar to patients and parents, the findings are more likely to apply to clinical practice, as they reflect the challenges and circumstances encountered in routine medical care. Furthermore, patients are more likely to adhere to treatment protocols involving medications they are familiar with or have easy access to through standard prescriptions, increasing the feasibility of recruitment and retention in the study.

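### Children judged non-compliant, or removed at investigator discretion, leave the study and not only the allocated strategy, on unblinded judgement, so outcome loss may differ by arm

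*Protocol article*

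**What the plan says.** The section Withdrawal of Participants and Criteria of Discontinuation of Study opens: "A study participant should be withdrawn from the study if at any time one of the following criteria applies". Two of its criteria matter here. One is "Severe compliance with study procedure as described in the protocol, as judged by the investigator", which makes sense only if non-compliance is meant. The other is open-ended: "Participants with any other condition or situation that, in the investigator’s opinion, may be valid for discontinuation from the study". The section does not separate ending the allocated strategy from ending follow-up, and the article describes no outcome collection after such a withdrawal.

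Strengths and Limitations confirms who is judging: "Without blinding, investigators and participants are aware of withdrawal allocation".

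The Intervention section sets different tasks for the arms. For gradual withdrawal: "Gradual withdrawal involves taking the prescribed applied dosage of the medication every other day over 14 days". For abrupt withdrawal: "Abrupt withdrawal indicates stopping the prescribed medication on the date of withdrawal initiation".

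Both arms share the calendar (Visits 2, 3, 4, and 5): "The participant will fill out a 14-day calendar of incontinent episodes before each visit". The symptom questionnaires also apply to both arms but on different schedules: "The number of times and when the participant must complete the questionnaire is dependent on the allocated withdrawal method". Secondary Outcome follows symptoms up to 30 days in the abrupt arm and up to 44 days in the gradual arm.

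Statistical Analysis models recurrence at 1 month, then at 3, 6 and 12 months among those still in the study. Sample Size Calculation allows at most 10% dropout, not split by arm.

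**The concern.** The rule tells sites to stop following a child because of a judgement made by someone who knows the allocation. The arms give different occasions for that judgement: only one has a dosing schedule, and the questionnaire burden differs. Removals could therefore be unequal between arms, or equal in number but different in kind.

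Unequal loss alone does not bias the comparison. Bias arises when the removed children's recurrence risk differs from that of the children who stay, and does so differently by arm. That is plausible for children who depart from the schedule or whose families are struggling.

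At stake is whether the trial compares the strategies as randomised. An analysis plan can choose an analysis set or an imputation method, but it cannot recover outcomes that the protocol told sites not to collect.

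**Working it through.** **Plan's own figure.** Inputs from Sample Size Calculation: recurrence 40% (abrupt) and 10% (gradual), significance level .05 (two-sided assumed), power 80%.

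n per arm = [1.96·√(2·0.25·0.75) + 0.842·√(0.40·0.60 + 0.10·0.90)]² / 0.30² = (1.200 + 0.483)² / 0.09 ≈ 31.5, rounded up to 32.

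That is 64 per pharmaceutical group. Then 64/0.9 = 71.1, giving 72, and 3 × 72 = 216. The stated size reproduces.

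**Power is not the issue.** If 7 of the 72 children in one drug group are lost, all from the gradual arm, power for that group is still 80.2%, against 80.6% at 32 per arm. Pooled power stays above 99%.

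**Bias, illustrated.** From the documents: 216 children, 108 per arm, and 10% loss (21.6, taken as 22). Assumed: all 22 lost are in the gradual arm (22/108 = 20% of that arm), there is no true difference, and recurrence is p = 25% in both arms. Let q be the recurrence risk among lost children. The gradual rate observed among the 86 retained is

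(108·p − 22·q) / 86.

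The rejection rate uses a normal approximation with d = 0.25 − observed gradual rate and SE = √[0.25·0.75/108 + g(1−g)/86], where g is the observed gradual rate: Φ(|d|/SE − 1.96) + Φ(−|d|/SE − 1.96).

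| q among lost | Observed gradual | Observed abrupt | Abrupt minus gradual | Rejection rate |
|---|---|---|---|---|
| 0% | 27/86 = 31.4% | 25% | −6.4 points | 17% |
| 25% | 21.5/86 = 25.0% | 25% | 0 | 5% |
| 50% | 16/86 = 18.6% | 25% | +6.4 points | 19% |
| 75% | 10.5/86 = 12.2% | 25% | +12.8 points | 65% |

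At a common 40% the range is −10.2 points (none of the lost recur) to +15.3 points (all recur).

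Equal numbers lost do not remove the problem. With 11 lost per arm at a common 25%, and recurrence among the lost of 75% (gradual) and 25% (abrupt), the observed rates are (27 − 8.25)/97 = 19.3% and (27 − 2.75)/97 = 25.0%, a difference of +5.7 points.

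The illustration uses all 108 children per arm, so it describes a comparison on the full randomised group. The later models use a smaller remaining population, and the document gives no figures from which to size the effect there.

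**Timing.** In Table 1 the first scheduled contact after day 0 is visit 2, day 30 ± 5. The gradual schedule ends at day 14. A 14-day calendar completed before a day-30 visit starts at about day 16. A child removed during the schedule would have no 1-month calendar. A child first judged at visit 2 may already have completed it, and then only months 3, 6 and 12 are lost.

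**The case against.** Several points on the other side stand.

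- A reader might infer that only the gradual arm can fail. That is true of dosing only. The criterion concerns study procedure, and children in either arm can miss calendars, calls or questionnaires. An abrupt-arm child can also depart from allocation by resuming the drug.
- No text says that losses differ by arm. The dropout allowance is one figure for all.
- The article describes no dosing check, and no call is scheduled before day 30. Losing the 1-month outcome needs an earlier unscheduled contact or a trigger such as missed questionnaires. The primary comparison is therefore less exposed than it first appears, and the later ones are at least as exposed.
- The article does not restrict the 1-month model to compliers. Analysis sets and missing-data rules may stand in documents not shown.
- A reader might infer a fixed bias in favour of gradual withdrawal. For example, if 10% or 20% of the gradual arm is removed and those children recur at 40% while the rest recur at 10%, the true risk is 0.9 × 0.10 + 0.1 × 0.40 = 13%, or 0.8 × 0.10 + 0.2 × 0.40 = 16%, against 10% observed. The arithmetic is right, but it is a single assumed scenario, and 3 to 6 points is small beside the planned 30. Other assumptions give no bias or the opposite sign.

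What these points leave untouched is the rule itself: withdrawal from the study, at any time, on unblinded judgement, with no statement that outcomes are still collected.

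**Conclusion.** The point holds as a design weakness with a possible consequence, not as a demonstrated bias. The criteria end study participation for non-compliance or open-ended opinion, judged with knowledge of the arm. Differences in dosing and questionnaire schedules make arm-related removal plausible. If removal also relates to recurrence, the 3-, 6- and 12-month comparisons are biased, and the 1-month comparison is too where removal precedes the calendar.

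Size and direction are undetermined. The range of about −6 to +13 points rests on three assumptions: 22 children lost, all from the gradual arm, and a common 25% recurrence. The document does not support saying that loss is tied to the arm, that the primary analysis becomes compliers-only, or that the bias favours gradual withdrawal.

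**What to change.** In Withdrawal of Participants and Criteria of Discontinuation of Study:

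- Correct the compliance criterion so that it reads as severe non-compliance.
- State that after investigator-initiated withdrawal for non-compliance or at discretion, the calls at 1, 3, 6 and 12 months and their 14-day calendars continue unless consent is withdrawn.
- State that these children are analysed as randomised, and that the reason for withdrawal is recorded and reported by arm.

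The change concerns outcome collection only. Handling of the medication stays with the protocol's clinical rules, and the separate recurrence criterion is not part of this point. Some children who neglect calendars will still have missing outcomes, so the change reduces the loss without removing it.

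The cost is a wording amendment and a little more follow-up for a few children, using calls already scheduled. The planned 216 is unchanged. With 25 children included by February 2025, 216 − 25 = 191 were still to be recruited at that date.
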